**Statistical Analysis**

Analysis will be by intention-to-treat using a repeated measures mixed modeling approach. Primary outcomes will be considered separately within each set (i.e., cognitive, wellbeing and productivity). Both univariate and multivariate analyses accounting for multiple comparisons and background variables will be conducted. Absence of any differences on primary outcome measures between ATO work location would lead to collapsing data across sites, otherwise SITE will be entered in the model as a covariate. For each analysis, within-subject change will be tested (TIME), followed by between GROUP differences, and then the main analysis will test the interaction between TIME X GROUP. Statistical significance will be set at alpha = 0.05. Treatment of missing values will depend on the extent and randomness of incomplete data.

Planned Subgroup analysis

A planned subgroup analysis of individuals categorized as high versus low on baseline cognitive testing (by median split of cognitive performance) will be conducted to determine if outcomes interact with initial level of cognitive competency.

Exploratory analysis

Depending on the nature of the results, exploratory structural equations modeling analyses may be run to determine the nature of any positive effects with respect to interactions between cognitive, wellbeing and productivity outcomes.

Power & Sample Size

Based on pilot study findings, effect size estimates for the domains of Memory and Executive function are presented in the table below. Note that positive effects are the desired direction for accuracy outcomes, and negative effects for response time outcomes. *Relative Effect Siz*e refers the Cohen’s d effect size in CCBT group (Pre-Post mean difference divided by pooled variance) minus the effect size in the control group.

|  |  | **Memory** | Executive Function |
| --- | --- | --- | --- |
| **Cohen's Relative Effect Size *d*** | **Accuracy** | 0.65 | 0.39 |
| **Response Time** | -0.51 | -0.99 |
| **Required Sample Size (n per group)** | **Accuracy** | 36 | 102 |
| **Response Time** | 66 | 22 |

Given the range of effect sizes observed, the most conservative effect size of 0.39 (on Executive accuracy scores) has been chosen. Controlling power at 0.8, 102 subjects would therefore be required per arm (rounded down to 100). After inflation for an expected 10% attrition rate, this results in an initial sample of N=220, (each arm to comprise n= 110).

References

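### Rounding 102 down to 100 and multiplying by 1.10 leaves 99 completers per arm and power of about 0.78, not 0.8; three table entries and the divisor of d also need correction

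*Protocol*

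**What the plan says.** All of this stands in the protocol under Statistical Analysis, Power & Sample Size.

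- **Design effect.** Pilot effect sizes are tabulated for memory and executive function, each for accuracy and response time. The smallest is used: "the most conservative effect size of 0.39 (on Executive accuracy scores) has been chosen".
- **Required number.** "Controlling power at 0.8, 102 subjects would therefore be required per arm (rounded down to 100". No reason is given for rounding down.
- **Attrition.** "After inflation for an expected 10% attrition rate, this results in an initial sample of N=220, (each arm to comprise n= 110". The Sample section repeats the total of 220.
- **Table.** For effect sizes of 0.65 and 0.39 (accuracy) and -0.51 and -0.99 (response time), the stated numbers per group are 36 and 102 for accuracy, and for response time "Response Time | 66 | 22".
- **Definition of d.** Each arm's effect size is described as "Pre-Post mean difference divided by pooled variance", and the control arm's value is then subtracted.
- **Significance level.** "Statistical significance will be set at alpha = 0.05". The protocol does not say whether tests are one- or two-sided.

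**The concern.** This paragraph is the protocol's only justification of the sample size, and it does not meet its own requirement. Rounding a required number down gives power away. Adding 10% to a target does not offset a 10% loss, because the loss is taken from the larger, inflated number; the target has to be divided by 0.9. The two steps act in the same direction.

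A reader who tries to reproduce the derivation meets two further obstacles. The four sample sizes do not follow from their effect sizes under one significance level and power. And a mean difference divided by a variance carries units, so it cannot enter a formula that expects a standardised difference. At stake is whether the stated power and the figures behind it can be reported as they stand.

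**Working it through.** **Inputs.** From Power & Sample Size: d = 0.39, power 0.8, 102 per arm rounded to 100, attrition 10%, 110 per arm. From Statistical Analysis: alpha = 0.05. From Design: 1:1 allocation. Assumption: two-sided test. A one-sided test would need 82 per arm and does not reproduce 102.

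**Step 1. Reproduce 102.** The normal approximation is n per arm = 2(1.960 + 0.842)²/d² = 15.70/d². At d = 0.39 this is 15.70/0.1521 = 103.2, so 104. The two-sample t-test gives 104.2, so 105. A d of 0.394, which prints as 0.39, gives 102 by t-test. The stated 102 is therefore reproduced to within rounding of d.

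**Step 2. Reproduce 220.** 100 × 1.10 = 110 per arm, and 2 × 110 = 220. The figure arises only by multiplying the rounded-down 100.

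**Step 3. Completers.** 110 × 0.90 = 99 per arm. Dividing instead:

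- from 100: 100/0.9 = 111.1, so 112 per arm (N = 224)
- from 102: 102/0.9 = 113.3, so 114 per arm (N = 228)

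**Step 4. Power with 99 per arm.** The noncentrality is d√(n/2) = 0.39 × √49.5 = 2.744. The normal approximation gives Φ(2.744 − 1.960) = 0.783; the noncentral t gives 0.779.

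| n per arm | d = 0.39 (t) | d = 0.395, upper limit of rounding (t) |
|---|---|---|
| 99 | 0.779 | 0.790 |
| 100 | 0.784 | 0.794 |
| 102 | 0.792 | 0.802 |

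No value of d that prints as 0.39 gives 0.80 with 99 per arm. Power of 0.80 with 99 per arm needs d = 0.400.

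**Step 5. The table.** Required n per group at two-sided 0.05 and power 0.8, rounded up:

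| d | Stated n | Normal | t-test | Power at stated n (t) | Stated n × d² | d that stated n implies (t) |
|---|---|---|---|---|---|---|
| 0.65 | 36 | 38 | 39 | 0.776 | 15.2 | 0.670 |
| 0.39 | 102 | 104 | 105 | 0.792 | 15.5 | 0.394 |
| 0.51 | 66 | 61 | 62 | 0.828 | 17.2 | 0.491 |
| 0.99 | 22 | 17 | 18 | 0.894 | 21.6 | 0.865 |

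Under one alpha and power, n × d² should be nearly constant, at about 15.7 to 16.7. The stated values run from 15.2 to 21.6. By the t-test, rounding of d can explain only the 102: the other three entries imply d values that do not print as the tabled ones. Two of the entries are too large and one is too small, so no single alternative alpha or power reconciles them.

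**Step 6. The divisor.** Cohen's d is a mean difference over a standard deviation. Since 102 is what an ordinary d of about 0.39 requires (Step 1), the pilot value was evidently used as an ordinary d, and the word variance is probably a slip.

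**The case against.** The shortfall is small, and part of it is disclosed. The protocol says openly that it rounds down. Against its own 102, the two steps together cost 0.792 − 0.779 = 1.2 percentage points at d = 0.39. This stands as a limit on the size of the point, but the text still claims power 0.8 for a number that does not give it.

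The planned analysis is an intention-to-treat mixed model with two follow-ups. A subject lost between the proximal and the longitudinal visit still contributes change to the first, and the protocol does not say when the 10% is lost. So 99 is the number with complete data, and the loss of information could be somewhat smaller. A subject with baseline data only adds little or nothing to the time-by-group contrast, so the model does not by itself remove the shortfall.

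The faulty table cells do not set N, and two of the three err on the large side. That is correct.

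Two stronger readings are tempting and are not supported:

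- **That the trial is seriously underpowered for change.** A reader might infer that d is scaled by the cross-sectional standard deviation, so that the number fits a comparison of change only if the test-retest correlation is about 0.5. The protocol does not say which standard deviation was pooled. Even if it were the cross-sectional one, the answer depends on the analysis. At 99 per arm and assumed correlations of 0.3, 0.5 and 0.7, an unadjusted change score gives 0.64, 0.78 and 0.94, but a baseline-adjusted contrast gives 0.82, 0.88 and 0.97.
- **That the sample size has no basis because d was divided by a variance.** The agreement of 102 with an ordinary d of 0.39 speaks against this.

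**Conclusion.** The point holds as a correction of stated figures. With 110 enrolled per arm and 10% lost, the plan has power of about 0.78 at d = 0.39, or at most 0.79 allowing for rounding of d, which is 1 to 2 percentage points below the stated 0.8. This assumes a two-sided 5% test, the full 10% lost to the comparison, and 0.39 as the standardised between-group difference on the scale of the test.

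The table entries 36, 66 and 22 are inconsistent with their effect sizes; the 0.39/102 entry that sets N is within rounding. The divisor of d is misdescribed, most likely in wording only. None of this shows that the trial is materially too small or that its sample size lacks a basis.

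**What to change.** 1. Keep N = 220 and replace the closing statement by, for example: with 110 per arm and 10% attrition (99 per arm), power is about 0.78 for d = 0.39, or 0.80 for d = 0.40 (two-sided alpha 0.05, two-sample t-test).
2. Recompute all four table entries with one named formula. By the two-sided t-test, from the d values as printed, they are 39, 105, 62 and 18 for d of 0.65, 0.39, 0.51 and 0.99. If the unrounded pilot d for executive accuracy supports 102, give it to three decimals.
3. Check the pilot calculation, then replace pooled variance by pooled standard deviation.

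The cost is text only: no extra participants, and a stated power that becomes slightly less favourable.
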